## Abstract

**Background:**

Clinical psychomotor skills training is a core component of undergraduate nursing education. Performing technical skills competently involves the use of cognitive and motor function. The training of these technical skills is typically carried out in clinical simulation laboratories. Peripheral intravenous catheter/cannula insertion is an example of a technical skill. It is the most common invasive procedure performed in the healthcare environment. Owing to unacceptable clinical risk and complications to patients, it is imperative that practitioners performing these skills are trained effectively to provide patients with best practice and high-quality care. Technologies identified as innovative teaching methods to help train students in this skill and in the skill of venepuncture include virtual reality, hypermedia and simulators. However, little high-quality evidence exists to confirm such educational approaches are effective.

**Methods/design:**

This study is a single-centre, non-blinded, two-group, pre-test and post-test randomised control trial. The randomised control trial will investigate whether a formal structured self-evaluation of videoed performance (experimental group) has an impact on nursing students’ peripheral intravenous cannulation knowledge, performance and confidence. The control group will also be videoed performing the skill but they will not view or self-evaluate their videoed performance. The peripheral intravenous cannulation procedures will be carried out in a clinical simulation laboratory using a task trainer. The data collection tools will be completed online using survey forms. Students will be randomised into the experimental group or into the control group using simple random sampling. The primary outcome measures the nursing students’ knowledge level of the skill of peripheral intravenous cannulation insertion. Secondary outcomes evaluate procedural competence and self-reported confidence and practices in the clinical environment.

**Discussion:**

This randomised control trial will investigate whether this pedagogical approach, using video modelling and self-evaluation, will positively influence students’ knowledge, confidence and performance in the skill of peripheral intravenous cannulation. Evaluating such teaching strategies using stringent methodologies may be impactful in influencing the training provided to healthcare practitioners.

**Trial registration:**

The randomised control trial detailed in this article is an educational research study and so does not fall under the ICMJE definition of a clinical trial as “any research project that prospectively assigns people or a group of people to an intervention, with or without concurrent comparison or control groups, to study the relationship between a health-related intervention and a health outcome”.

**Supplementary Information:**

The online version contains supplementary material available at 10.1186/s13063-023-07200-8.

## Background

Learning clinical psychomotor skills is an integral part of student learning [1, 2]. Performing procedural skills competently involves the student to use cognitive and motor functions. Nurse educators are challenged to deliver student-centred active learning strategies, to prepare students for practice. In doing so educators effectively incorporate cognitive skills with technical skills with the intention to boost self-confidence and efficacy in those skills [3]. They are challenged to prepare nursing students to provide safe and competent care, as it is noted that the care a patient receives is linked to the competence and performance of nurses [4]. In nursing education these technical skills are taught in clinical laboratory settings. This setting is the foundation of safe patient care [5] and the benefits of clinical skills laboratories are well documented and are integral in the teaching of procedural skills [6].

The insertion and management of a peripheral intravenous catheter/cannula (PIVC) is an important nursing task [7]. They are the most commonly used invasive device and up to 70% of patients need a PIVC during their hospitalisation [8]. The procedural task is performed in order to provide patients with intravenous fluids and/or medication [9]. Although PIVCs are a globally common invasive procedure their premature failure, leading to their removal and replacement is also very common [10, 11]. The insertion, management and removal of a PIVC can have negative experiences for patients and there is a need for the procedure to be improved and to adhere with recommended clinical guidelines [11]. However, there are inconsistencies between recommended practice and reported practice [10]; Cooke et al. highlight that in order to provide best practice and quality care, it is paramount to produce effectively trained practitioners [11]. Nurses should receive appropriate training incorporating knowledge and application of psychomotor skills and thereafter be supervised in their practice in order to become competent in intravenous cannulation [7]. Currently, Irish PIVC training standards include a hybrid learning model. The programme includes both the theoretical and practical components [12]. Published as a national training standard it was recently expanded to include the undergraduate nursing and midwifery curriculum [13]. The practical component of PIVC insertion includes an observation and demonstration session in a clinical skill laboratory/simulation environment [12].

Recent studies regarding the teaching of PIVC and venepuncture have been noted to use innovative teaching methods such as web-based learning or tools [1, 14, 15], hypermedia [16], simulators [5, 9, 17, 18], video-assisted teaching [18], virtual reality [19], video-assisted debriefing [20] and a vein visualisation display system using near-infrared light [21]. An integrative review regarding the teaching of venepuncture similarly identified technologies such as e-learning courses, videos and demonstrations combined with manikins or haptic devices [22].

This proposed study will determine if video technology can assist with improvements in the teaching and assessment of PIVC insertion in an undergraduate nursing student cohort.

As a teaching method, video modelling is the use of video recordings which target particular skills and it allows students to view their own performance. The intention is to increase learning by evaluating areas which need improvements or adjustments [23]. One of the goals of this proposed study is to use a teaching strategy which can promote student-centred, active learning to improve the student’s competency in the clinical skill of intravenous cannulation. Combining video recording and reflection may be an effective teaching strategy for learning clinical skills [23]. Studies using quasi-experimental, surveys and descriptive and interpretive designs report the beneficial use of video modelling to teach clinical skills. They include the development of self-evaluation, reflection and skill performance [24]. It can assist in promoting the student’s self-awareness [23, 25], which is noted to improve clinical skills competency [25]. Students reviewing and reflecting on their performance are playing an active role in their learning. As a result, their clinical skill competency can be enhanced, and it can promote self-directed learning.

A more detailed overview of such studies includes first year midwifery students self-recorded and assessed their videos of selected midwifery practice skills. The study found that this provided an accessible option for assessing competency, self-reflection and re-recording to master their skill [26]. Comparing the effect role-playing and video feedback has on learning cardiopulmonary resuscitation, the study noted that the mean difference between the psychomotor and cognitive learning scores before and after training in the video self-feedback group was significantly higher [27]. Another study focused on the skills of intramuscular injections and suction and evaluated the effectiveness of using video recording and self-evaluation [28]. The experimental group, who self-practised, video-recorded and self-evaluated the skill had statistically significantly better performance in nursing skills and confidence in comparison to the traditional group, of lecture and demonstration. Similarly, Cernusca, Thompson and Riggins (2018) identified that the use of iPad videos appears to be an effective teaching tool, regarding learning sterile procedures, for students to assess their performance and reflect on areas which need development [23]. A study on self-evaluation of performance videos, which focused on urinary catheterisation, noted that self-evaluation of performance videos was effective and students in the experimental group demonstrated higher competency in the skill, their communication skills and their motivation to learn. It appeared to positively influence students’ retention of knowledge as they actively participated in their learning [25].

Previous study findings give validation for conducting this research study. A recent systematic review on the effect of video on psychomotor skills in nursing noted that video would be a good addition to teaching and learning clinical skills [2]. Although the use of video is not novel, it does not appear to have been studied in the context described in our study. Corroborating our stance that our proposed study was not carried out previously on this topic, a systematic review [2] did not appear to identify a randomised control trial study whereby students reviewed their own intravenous cannulation videos. Creating a safe and controlled environment for students in order for them to learn and practice their psychomotor skills, which are required to become a competent practitioner, is the responsibility of nursing programmes [25].

The aim of our study is to evaluate the effectiveness of structured self-evaluation of video-recorded simulation practice on nursing students’ PIVC knowledge, confidence and performance. Outcome measures will focus on procedural knowledge, procedural competency and students’ confidence in the skill. Alongside clinical outcomes regarding students’ successful and unsuccessful attempts and feedback on their performance of the skill will be investigated in this study. Our study is designed to assess the use of video technology in order to provide students with practice opportunities and to promote directed learning which the student can carry out independently. It does not wish to increase the educator burden. The results of the study will assist educators in designing and developing a data-informed curriculum on PIVC care and insertion.

## Objectives

### Research hypothesis

Formal structured self-evaluation of videoed performance has a positive impact on nursing students’ peripheral intravenous cannulation knowledge, performance and confidence.

### Study objectives

The primary objective of this study is to compare the effect of structured self-evaluation of video-recorded performance on students’ knowledge of peripheral intravenous cannulation to students who do not formally self-evaluate their videoed performance.

Secondary objectives include comparing the effect of structured self-evaluation of video-recorded performance on students’ skill performance, their confidence levels and the success of their attempts in clinical practice to students who do not formally self-evaluate their videoed performance.

## Methods

### Study design

The study protocol has been prepared and is reported in accordance with the SPIRIT PRO extension reporting guidelines [29]. This study protocol describes a single-centre, non-blinded, two-group, pre-test and post-test randomised control trial. It is not possible to blind students to their randomisation due to the nature of the study. The study design is open label with only outcome assessors being blinded.

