### Eligibility criteria

Students will be asked to consent onto the study by signing an informed consent form prior to participating in any study interventions/data collection. The informed consent will be taken by the primary researcher with the support of the wider research team. On the consent form, students are asked to consent to the study results being shared with the affiliated School of Nursing and Midwifery, and training hospitals and that results may be published. This trial does not involve collecting biological specimens for storage. Study eligibility criteria can be noted in Table 1.

**Table 1 Tab1:** Study eligibility criteria

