#### Experimental group

The experimental group will receive current education standards however they will have two more simulated practices. These extra practice sessions will be video recorded. After completing their extra practice students will provide feedback to the researcher on how they perceived the practice session. Students will then get the opportunity to view their video-recording and complete a self-evaluation checklist and update the researcher on any feedback they may have after viewing their performance and completing the task-specific checklist. The performance will be evaluated by the researcher. This process will be repeated for the students’ second practice session a number of weeks later. Students in this group will complete a knowledge, attitude and practices (KAP) survey prior to their first practice session (pre-test) and after their second practice session (post-test). Students will complete a clinical outcomes survey, evaluating their practices in the clinical environment, throughout the study.

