#### Implementation

The primary researcher will implement the randomisation process. As the researcher will not be involved in teaching the students and will not be familiar with the students, this will reduce the risk of bias. All students will be allocated to their randomised group at the same time, students cannot be randomised at the time of consent as the research team will be unaware of the overall study sample size. Therefore, to ensure equal allocation as best as possible, randomisation will not be completed until every participant has consented. The allocation list will be kept electronically and only available to the research team. However, the allocation details of each participant are not confidential as students will know their allocated group.

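### Assessor blinding is claimed, but the described procedures give the scorer of procedural competence arm-revealing information

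*Protocol article*

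**What the plan says.** The Study design section of the protocol article explains that students cannot be blinded and adds: "The study design is open label with only outcome assessors being blinded".

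Three other places describe who handles what:

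- **Experimental group.** After each recorded practice the student tells the researcher how the session seemed. Then: "Students will then get the opportunity to view their video-recording and complete a self-evaluation checklist and update the researcher on any feedback". The next sentence is "The performance will be evaluated by the researcher". The cycle is repeated at a second session some weeks later.
- **Control group.** The sequence is the same except that there is no viewing and no self-evaluation. The researcher again evaluates the performance.
- **Implementation (Randomisation).** "The primary researcher will implement the randomisation process", and "The allocation list will be kept electronically and only available to the research team". The section adds that allocation is not treated as confidential, because students know their group.

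The Task-specific checklist section says that researchers score the videos with the checklist used by experimental students for self-evaluation. It adds that the researchers' evaluations will be compared with the students' own.

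**The concern.** Procedural competence is a secondary outcome, and skill performance is named in the research hypothesis. Some checklist content needs judgement, such as whether asepsis was maintained. A scorer who knows the arm, or has just heard a student describe what went wrong, can mark such items differently without intending to.

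Assessor blinding matters most for this outcome. Knowledge, confidence and clinical practices come from surveys completed by students who know their group, so a blinded rater cannot protect them. Performance is scored from a recording, and there blinding is feasible. If the claim stands while the procedures contradict it, readers will judge the risk of bias for this outcome on a safeguard that was not in place.

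**Working it through.** No figure is attached to the blinding claim, so the check sets the sections side by side. The sample size was calculated for the knowledge score and does not depend on this point.

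**1. Who scores.** The Experimental group and Control group sections both give the evaluation to the researcher. The Task-specific checklist section uses the plural, researchers. No section describes a separate rater.

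**2. What reaches that role, by arm.**

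| Information given to the researcher | Experimental | Control |
|---|---|---|
| Feedback straight after the practice | Yes | Yes |
| Feedback after viewing the video and completing the checklist | Yes | No |
| Self-evaluation to compare with the researchers' scores | Yes | None exists |

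The first row does not separate the arms. The second and third rows do, because each exists in one arm only.

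**3. Timing.** Randomisation precedes both sessions. In the experimental arm the first viewing comes after the first practice, so the second session is the first performance that can reflect self-evaluation. By then the researcher has already received the post-viewing feedback from session 1. Even if each video were scored before that session's feedback was taken, the session 2 score would still be given by someone to whom the arm had been revealed. Session 2 is where any effect on performance would appear.

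**4. The allocation list.** The Implementation section makes the list available to the research team and excludes no one. A scorer drawn from the team therefore has access to it, whoever ran the randomisation.

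**5. Comparison with self-evaluations.** This comparison does no harm if it is made after the researchers' scores are fixed. The article does not set that order.

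**6. Safeguards described.** The article mentions no coding of videos, no scorer outside the sessions, and no withholding of the list, feedback or self-evaluations.

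Step 2 together with step 3 is enough for the conclusion. Step 4 supports it independently.

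**The case against.** The strongest reply is that a condensed article need not describe how videos are coded or who rates them, and that the full protocol, available on request, may name a blinded rater. The plural in the Task-specific checklist section leaves room for one. This would answer a complaint about silence. It does not answer the text that is present, which gives the scoring to the researcher who receives the arm-revealing feedback. If a separate rater exists, those sections still need correcting.

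Several stronger readings are tempting and are not supported:

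- **That the person who randomises also scores.** A reader might infer this because the Implementation section goes on to call the primary researcher simply the researcher. No section says the two are the same person.
- **That the trial contradicts itself by its label.** The Study design section says "This study protocol describes a single-centre, non-blinded, two-group, pre-test and post-test randomised control trial", but it explains in the same paragraph that students are unblinded and assessors blinded. This is loose wording.
- **That taking consent makes the randomiser familiar with the students.** The Eligibility criteria section says "The informed consent will be taken by the primary researcher with the support of the wider research team". The statement about familiarity follows one about not teaching the students and most naturally means no prior relationship. All students consent before a single sort of random numbers, so contact at consent cannot steer allocation. It also has no bearing on who scores the videos.
- **That the knowledge score is exposed through open-ended survey answers.** The Data analysis section sends open-ended answers to qualitative coding, and nothing says they enter the knowledge score.
- **That a false-positive rate can be quoted.** It would require an assumed size of rater bias, for which the document gives no basis, and a test for checklist scores that the document does not specify.

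**Conclusion.** The point holds as a contradiction within the protocol article. Followed as written, the assessor blinding claimed in Study design is not delivered for video-scored procedural competence.

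Its reach is limited to that one secondary outcome. The primary outcome is knowledge, taken from a survey the students complete online, and its ANCOVA uses no video score, so it is not shown to be affected. The size and direction of any bias cannot be derived from the document.

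The conclusion assumes that the researcher in the Experimental group section is one role throughout, as consecutive sentences there suggest. It does not need the scorer to be the person who randomised. This should be fixed, but it does not undermine the primary analysis.

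**What to change.** Reconcile the Study design section with the Experimental group, Control group, Implementation and Task-specific checklist sections:

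1. Relabel all videos with random codes and shuffle both arms and both sessions together before scoring.
2. Give the scoring to an existing team member who does not run the sessions or take feedback, and state that this person has no access to the allocation list.
3. Withhold feedback and self-evaluations from that person until the scores are locked. Compare researcher and student evaluations only after that.
4. If no team member can be kept unaware, delete the statement that assessors are blinded and report performance as an open-label outcome.

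The randomisation procedure and the handling of the knowledge survey need no change for this purpose.

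The cost is some file relabelling and a delay, because scoring waits until both sessions are filmed. No new staff are needed if a suitable team member is available. At the stated protocol version data collection had not begun, and because performance is recorded, coded scoring can be arranged without altering the sessions.

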### Study setting and participants

The study interventions and data collection will be performed online and in a simulated clinical skills laboratory. The student group will be final year nursing students registered in a nursing programme in one Irish university.

### Eligibility criteria

Students will be asked to consent onto the study by signing an informed consent form prior to participating in any study interventions/data collection. The informed consent will be taken by the primary researcher with the support of the wider research team. On the consent form, students are asked to consent to the study results being shared with the affiliated School of Nursing and Midwifery, and training hospitals and that results may be published. This trial does not involve collecting biological specimens for storage. Study eligibility criteria can be noted in Table 1.

**Table 1 Tab1:** Study eligibility criteria

**Inclusion criteria**
Final year nursing students in the participating university
Final year nursing students who have completed the formal training required on the skill as per national curriculum standard requirements
